***Analysis populations***

There will be the following analysis populations for this study:

- 1) Modified Full Analysis Set (mFAS): All patients who are randomized into the study and who have received the investigational product (any of the 2 arms treatment) will be included in the mFAS population. The accepted exclusions, as per the ICHE9, are predefined as follows:

- Participants who fail to satisfy an entry criterion may be excluded from the analysis without the possibility of introducing bias only under the following circumstances:

- i) The entry criterion was measured prior to randomization;
- ii) The detection of the relevant eligibility violations can be made completely objectively;
- iii) All participants receive equal scrutiny for eligibility violations;
- iv) All detected violations of the particular entry criterion are excluded.

- 2) Per Protocol Population: Per protocol (PP) patient sets will be defined as those patients included in the mFAS set without major protocol deviations that might impact the study's main assessments. These deviations will be assessed during the data review prior to database lock.

- 3) The Safety population is defined as all randomized participants who received the investigational product (any of the two arm treatment). In this study the Safety population will have the same definition than the mFAS subset and thus, all safety analysis will be conducted on the mFAS population.

The primary analysis set for the main analyses will follow the ‘*ICH Topic E9 - Statistical Principles for Clinical Trials*’ (CPMP/ICH/363/96)‘ and will be based on the modified full analysis set (i.e. ITT or mFAS; see beginning of section 0, above).

However, the main outcome will be also analysed using the PP set for sensitivity purposes.

The precise reasons for excluding participants from each population will be fully defined and documented independently of the randomization codes during the data blinder review and before data lock.

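### The protocol equates the safety population with the mFAS, yet the mFAS may lose treated patients for eligibility violations, so exposed patients could drop out of the safety analysis

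*Protocol*

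**What the plan says.** The wording is all in the protocol, section 9, under Analysis populations.

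- **Item 1, mFAS, starting definition:** "All patients who are randomized into the study and who have received the investigational product", in either arm.
- **Item 1, exclusions:** the same item continues with "The accepted exclusions, as per the ICHE9, are predefined as follows" and then "Participants who fail to satisfy an entry criterion may be excluded from the analysis". Four conditions must hold: the criterion was measured before randomisation, the violation can be detected wholly objectively, all participants get the same scrutiny, and "All detected violations of the particular entry criterion are excluded".
- **Item 3, safety, definition:** "The Safety population is defined as all randomized participants who received the investigational product", again in either arm. No exclusion is attached.
- **Item 3, safety, equation with the mFAS:** "In this study the Safety population will have the same definition than the mFAS subset", from which the protocol concludes that "all safety analysis will be conducted on the mFAS population".
- **Closing paragraph:** "The precise reasons for excluding participants from each population will be fully defined and documented independently of the randomization codes", to be done at the data review before lock.

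Adverse events are a named secondary outcome (section 6.2.2).

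**The concern.** Item 3 gives two descriptions of the safety set. By its opening sentence, the set is everyone treated. By the sentence that assigns the analysis, it is the mFAS, which item 1 allows to be smaller. The two agree only if the eligibility exclusion is never used.

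Excluding ineligible patients under strict conditions can be defended for an efficacy analysis. It has no matching rationale for safety, where the question is what happened to the people who took the drug. A programmer who builds the adverse event tables on the mFAS as written would omit any treated patient removed for an eligibility breach, from numerator and denominator alike. With 35 patients per arm, the tables have little room for unexplained losses.

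This is not a detail that can be left to the SAP, because the protocol itself fixes the conflicting rule. An SAP that follows it inherits the conflict, and one that corrects it departs from the protocol.

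**Working it through.** **1. Compare the sets.** Let T be all randomised patients who received treatment in either arm, and E the members of T removed under the eligibility rule.

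- Safety, by its own definition: T.
- mFAS, by its definition including the exclusions: T without E.
- Set assigned to the safety analysis: the mFAS, so T without E.

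The two coincide only when E is empty.

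**2. Can E be non-empty?** Yes. None of the four conditions requires that the patient was untreated. Moreover, untreated patients are already outside the mFAS by its starting definition, so the eligibility rule can only ever change the set by removing treated patients.

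**3. Which criteria could trigger it?** From sections 7.2 and 7.3, those recorded before randomisation and open to objective checking include RF/ACPA status, age, disease duration, radiographic erosions, previous DMARD use and recent steroid use. Contraindication to a study drug is also listed. It will often need clinical judgement, so it may fail the objectivity condition, in which case such patients would stay in the mFAS.

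**4. Size per patient.** The planned numbers are 35 per arm and 70 in total (sections 7.1 and 9). If all are treated:

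- one excluded patient: 1/35 = 2.9% of an arm, or 1/70 = 1.4% of the trial;
- five excluded patients: 5/70 = 7.1% of the trial.

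The protocol does not say how many might be excluded. The range of one to five is an assumption.

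**5. Direction.** Suppose, as an assumption for illustration, that 2 of 35 patients in an arm have a serious adverse event, 2/35 = 5.7%. Remove one patient:

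- if that patient had the event: 1/34 = 2.9%;
- if not: 2/34 = 5.9%.

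The rate may fall or rise, depending on who is removed.

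**6. Chance that an event is left out.** With k excluded patients and an assumed independent per-patient risk p of a given adverse event, the chance that at least one such event is omitted is 1 − (1 − p)^k.

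| k | p = 5% | p = 20% |
|---|---|---|
| 1 | 5% | 20% |
| 5 | 1 − 0.95^5 = 23% | 1 − 0.80^5 = 67% |

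The values of p are assumptions too. The table shows only that the loss need not be trivial if the rule is used.

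**7. What is not touched.** The protocol gives no figure on this point to reproduce. Its sample size stands apart: exact power of Fisher's test at 35 per group, for 42% versus 11% and two-sided 0.05, is 79.6% against the stated 80%. Neither that nor the primary test depends on the safety set. Section 10 collects and reports serious and non-serious events without reference to any analysis population.

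**The case against.** The strongest reply is that the intent is plain. The safety definition covers everyone treated, the mFAS item opens in almost the same words, and the statement that the two share a definition rests on that common opening. On this reading the exclusions belong to efficacy only, and safety covers all exposed patients. The exclusion is also optional and bound by four conditions, eligibility is checked at visit 1 before randomisation at visit 2 (section 8.8), and there may be no treated violators at all.

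Much of this stands. The likely intent is an all-treated safety set, and the effect is nil if no treated patient is excluded. But the milder reading is not written down. The exclusions sit inside the mFAS definition, the analysis they refer to is not limited to efficacy, and the closing paragraph foresees exclusions from each population. A literal application gives the smaller set.

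A reader might go further and infer that the protocol plans to remove exposed patients, that those removed would be the ones most at risk, such as patients with a contraindication, and that harm would therefore be understated. The documents do not support this. Exclusion is permitted, not planned. A contraindication may not meet the objectivity condition, while several of the criteria that meet it easily, such as serostatus, erosions, age and disease duration, mainly define the disease population. The direction of any change in rates is open, as step 5 of the working shows.

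**Conclusion.** The conflict is real, and the rule is wrong as written. The protocol defines safety as all treated patients and then assigns every safety analysis to a set from which treated patients may be removed. If the optional exclusion is used on a treated patient, that patient's exposure and events leave the population-level safety analysis.

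The size cannot be stated in advance. It is 2.9% of an arm per excluded patient, assuming 35 treated per arm, with an unknown number excluded and no fixed direction for the effect on rates. It is zero if the exclusion is never applied. It would be a mistake to read this as a gap in safety surveillance, because individual events are still collected and reported under section 10. Only the summary analysis is exposed. On that footing the point is of moderate severity: worth correcting before database lock, but no threat to the primary result.

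**What to change.** In section 9, Analysis populations, item 3, delete the sentence that equates the safety population with the mFAS and moves the safety analyses to it. Replace it with a statement that all safety analyses use every randomised participant who received at least one dose of either study treatment, and that nobody is removed from this set for an eligibility violation. Carry the same wording into the SAP. The mFAS and its exclusions can remain as they are for efficacy.

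The cost is one sentence in each document. No extra data, visits or patients are needed, and the change restores the definition with which item 3 already opens.

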### ***Subgroup analysis***

The subgroups will be prospectively identified in the SAP. In case of any post-hoc subgroup analysis, they will be justified and identified as data-driven and, they will follow the principles and regulatory recommendations.

### ***Adjusted analysis***

The **main planned analysis** will be unadjusted and any deviation from this plan will be traced and identified in the SAP and/or the final report.

### ***Statistical tests***

The Fisher’s exact test used for categorical variables, the t-test or the one-way ANOVA for Gaussian distributed variables (for 2 or more than two groups, respectively) and for non-Gaussian continuous variables, non-parametric methods (Mann- Whitney test for two groups or Kruskal-Wallis for more than two groups). A detailed description of tables and tests for each variable will be documented upfront in the SAP.

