#### **6.2.2 Secondary outcomes:**

- Clinical efficacy: frequency and intensity of joint attacks
- Adverse events
- Effects on ACPA titres, fine specificities and isotypes: Citrullinated peptides derived from fibrin, vimentin and alpha-enolase and IgG, IgM and IgA will be used. ACPA fine specificities will be measured by home-made ELISA tests according to the procedure recently described by our research group (Cabrera-Villalba S et al. Arthritis Res Ther, 2017; 19(1):141). All tests will be carried out

at baseline, and at 3, 12 and 24 months of follow-up. Serial measurements of serum RF are not considered

- Effects on anti-CarP antibodies (home-made ELISA): chemically carbamylated fetal calf serum or fibrinogen proteins will be prepared and used as antigens according to the procedures described by Shi et al. *PNAS USA* 2011, 108: 17372-7 and Scinocca et al. *J. Rheumatol.* 2014, 41: 270-9). Doubly modified (homocitrullinated and citrullinated) peptides derived from several proteins present and the inflamed synovium, recently developed in our group (unpublished results), will also be used as antigens. Anti-CarP will be measured at baseline and, in antiCarP positive patients, at 3, 12 and 24 months of follow-up.

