## **8.2.SCREENING (VISIT 1)**

Visit schedule screening will entail evaluation of:

- Inclusion and exclusion criteria
- Demographic data including age, gender and medical history
- Characteristics of PR
  - o Number of joint attacks (per month)
  - o Intensity of attack (analogue scale 0-10 cm)
  - o Presence of inflammation during attacks (swelling, eritema)
- Clinical examination
- Concomitant drugs
- Joint assesment
- Routine blood test ( include at least CRP, ESR Hb, WBC, platelets, cholesterol, ALT/AST, creatinine)
- Rheumatoid Factor
- Anti-CCP.

Hand and feet radiographs (: unless an X-ray was performed < 6 months)

-

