**All** patients included after the screening will be followed until month 24. Visits will be performed every three months according to standard clinical practice. In each visits the achievement of the RA classification criteria will be analysed. The

frequency, duration and intensity (in a visual analogue scale) of the joint attacks will be analysed together with the presence of joint swelling or erythema.

Concomitant therapy will be recorded . Systemic steroids (oral or parenteral) in an equivalent dose higher than 7.5 mg/day of prednisone are not permitted during the study.

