## **8.9 END OF STUDY TRIAL DEFINITION**

The end of the study trial will be triggered 6 months after the last recruited patient completed final study visit (Last Patient Last Visit LPLV). This additional months will allow to monitoring and statistical analysis .

Those patients who achieve the classification criteria of RA at any time during the 24 month of the trial are considered non responders and will discontinued the study protocol and treated according to physician criteria.

Whenever possible, patients will be followed by entering their data in the CRd until the end of 10 visits

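### For continuous outcomes the protocol names only unadjusted two-group tests, although baseline attacks and ACPA are collected, and it does not say how values after progression to RA enter the comparison

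*Protocol*

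**What the plan says.** **Tests.** Section 9, Statistical tests, sorts methods by type of variable. Categorical variables get Fisher's exact test. Continuous variables get "the t-test or the one-way ANOVA for Gaussian distributed variables (for 2 or more than two groups, respectively"), or Mann-Whitney/Kruskal-Wallis if not Gaussian. The paragraph closes with "A detailed description of tables and tests for each variable will be documented upfront in the SAP".

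**Adjustment.** Section 9, Adjusted analysis, says that the main planned analysis "will be unadjusted and any deviation from this plan will be traced and identified in the SAP and/or the final report". It says nothing about secondary outcomes.

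**Data collected.** Section 8.2 records at screening "Number of joint attacks (per month") and "Intensity of attack (analogue scale 0-10 cm"). Section 8.8 adds that at the three-monthly visits "frequency, duration and intensity (in a visual analogue scale) of the joint attacks will be analysed". Under section 6.2.2 the ACPA tests are done "at baseline, and at 3, 12 and 24 months of follow-up".

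**Progression.** Under section 8.9, patients who meet the RA criteria "will discontinued the study protocol and treated according to physician criteria". The next sentence asks that patients' data still be entered through visit 10 where this can be done.

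**Missing data.** The only explicit rule in section 9 counts a missing primary outcome as a failure. For the rest it cites the ICH E9 and European missing-data guidelines and refers to the SAP.

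**The concern.** Attack frequency and intensity carry the clinical-efficacy objective. The ACPA outcomes are the evidence for the proposed mechanism, a change in the B-cell response. All three have a pre-treatment value and repeated later values, and the trial has only 35 patients per arm. A two-group test at one visit discards the baseline and the intermediate visits.

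The named tests also ignore observation time. The arms are expected to differ greatly in how many patients leave the study protocol on reaching RA. A count of attacks over unequal follow-up, or a month-24 titre that is partly absent and partly measured under another treatment, is hard to interpret without a stated rule.

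Finally, letting the shape of the data decide between a t-test and a rank test leaves open whether means or ranks are compared.

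**Working it through.** **1. The plan's own figure.** The protocol assumes 2-year progression of 42% and 11%, two-sided alpha 0.05, 80% power and Fisher's exact test, and gives 35 per group. Full enumeration at 35 per group gives 79.6% power, so the figure reproduces. It concerns the primary endpoint only; the rates and group size are used below.

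**2. Precision lost by ignoring baseline.** Let r be the correlation of baseline with follow-up. The documents give no value, so r is an assumption, and equal variances at both times are assumed. Relative to the variance of a raw follow-up comparison:

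- baseline-adjusted (ANCOVA): 1 − r²
- change from baseline: 2(1 − r)
- ANCOVA against change score: (1 − r²) / [2(1 − r)] = (1 + r)/2

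| r (assumed) | ANCOVA vs raw follow-up | Variance cut | Equivalent n per arm, 35/(1 − r²) | ANCOVA vs change score | Variance cut |
|---|---|---|---|---|---|
| 0.3 | 0.91 | 9% | 38 | 0.65 | 35% |
| 0.5 | 0.75 | 25% | 47 | 0.75 | 25% |
| 0.7 | 0.51 | 49% of variance removed | 69 | 0.85 | 15% |

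The exact entry for r = 0.7 against raw follow-up is 1 − 0.7² = 0.51 remaining, so the cut is 49%.

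In power terms (noncentral t, 35 per arm), a raw follow-up t-test has 54% power for a 0.5 SD difference. Adjustment raises this to 58%, 66% and 82%. The difference detectable with 80% power falls from 0.68 SD to 0.65, 0.59 and 0.49 SD.

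**3. How many patients progress.** At the protocol's rates:

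- hydroxychloroquine: 35 × 0.42 = 14.7 progress; 35 × 0.58 = 20.3 remain RA-free
- abatacept: 35 × 0.11 = 3.9 progress; 35 × 0.89 = 31.2 remain RA-free

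So about 15 against 4 patients leave the study protocol, most of them in one arm. Their later values are either missing or obtained under physician-chosen treatment.

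**4. What the missing rule could cost (illustration, not the plan).** Suppose late tests used RA-free patients only and there were no true effect on attacks. Let attack activity be standard normal with correlation ρ (assumed) to a normal liability for progression. The mean among non-progressors is −ρ φ(z)/(1 − p), where z is the (1 − p) normal quantile.

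- p = 0.42: φ(z)/(1 − p) = 0.391/0.58 = 0.674
- p = 0.11: φ(z)/(1 − p) = 0.188/0.89 = 0.211
- spurious difference: (0.674 − 0.211)ρ = 0.463ρ, that is 0.14 SD at ρ = 0.3 and 0.32 SD at ρ = 0.7, favouring hydroxychloroquine

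With 20 and 31 patients and the SD held at 1, the false-positive rate would be about 8% to 20% instead of 5%.

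**The case against.** The strongest reply is that nothing is fixed here. The Statistical tests paragraph is a generic list, names neither attacks nor ACPA, does not say whether the test applies to follow-up values or to change, and hands the choice per variable to the SAP. This stands: a change-score or adjusted analysis is not excluded. But the methods the protocol does name include none that adjusts for baseline or accounts for observation time, so a SAP that follows it literally would inherit the weakness.

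A reader might infer from the Adjusted analysis paragraph that the secondary outcomes must be analysed unadjusted. The text does not support this; it speaks of the main planned analysis only.

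A reader might also infer that month-24 comparisons are meant to include only patients who have not progressed. That is not the plan either. Section 8.8 has all included patients followed to month 24, section 8.9 asks for data to visit 10 where possible, specific blood tests are scheduled at treatment cessation or early withdrawal, and the primary analysis set is the mFAS. The 20 against 31 figure counts expected non-progressors; it is not an analysis set.

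It is also fair to say that an unadjusted comparison of randomised groups with complete data is valid, only less precise, and that the gain rests on an assumed correlation. At r = 0.3 the gain over raw follow-up is 9%.

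**Conclusion.** The point holds in a limited form. For continuous outcomes the protocol names only unadjusted two-group tests, although the baseline values needed for a better analysis are already collected. The cost is precision: from 9% of variance at r = 0.3 to about half at r = 0.7 (0.51 remains) against raw follow-up, and 35% down to 15% over the same range against a change score. All of this depends on r, which the documents do not give.

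Separately, with about 15 against 4 patients expected to progress, late attack and ACPA comparisons will be either selectively incomplete or mixed with post-progression treatment. The protocol does not say which is intended, and the named tests do not handle unequal observation time. The bias figures illustrate one possible handling and are not a forecast.

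Only secondary outcomes are concerned. The sample size and the primary Fisher comparison stand.

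**What to change.** In section 9, Statistical tests, replace the distribution-driven choice between t-test and Mann-Whitney for these outcomes, and carry the same wording into the SAP:

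- **ACPA titre (log scale) and attack intensity:** ANCOVA, or a repeated-measures model with arm, visit and arm-by-visit terms, adjusted for the baseline value.
- **Attack frequency:** a count model, for example negative binomial, with baseline attack rate as covariate and log observation time as offset.
- **Values after RA progression:** state whether they are included as observed whatever the later treatment, or whether the comparison stops at progression, and what question each answers. If they are included, the data entry through visit 10 that section 8.9 requests becomes essential for these outcomes too.

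A sensitivity analysis ranking progressors worst is optional.

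The cost is protocol or SAP wording and a little more programming; the planned visits already supply the data. The downside is some reliance on model assumptions in a sample of 70.

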### ***Interim Analysis and multiplicity adjustments***

---

 EMA/CHMP/EWP/117211/10. Guideline on the investigation of subgroups in confirmatory clinical trials (Draft). URL: [http://www.ema.europa.eu/ema/index.jsp?curl=pages/regulation/general/general\\_content\\_001215.jsp&mid=WC0b01ac05807d91a4](http://www.ema.europa.eu/ema/index.jsp?curl=pages/regulation/general/general_content_001215.jsp&mid=WC0b01ac05807d91a4), last access: 30-Oct-2017.

The purpose of this interim analysis is not to stop the study due to efficacy, which is assessed at 24-month follow-up. It is a descriptive evaluation of the early response, at 12 months of follow-up. There is only one primary outcome in this trial. Therefore, no multiplicity adjustment will be implemented to perform this analysis and p-values will be considered descriptive at their nominal value.

The analysis will follow the principles specified in the ICH E9 and the CPMP/EWP/908/99 Points to Consider on Multiplicity issues in Clinical Trials guidelines. .

#### ***Procedures to account for missing or spurious data***

The handling of missing data will follow the principles specified in the ICH-E9 and the CPMP/EWP/1776/99 Rev1. Guideline on Missing Data in confirmatory trials Guidelines. Patients with missing data for the primary outcome will be considered as failures irrespectively to the drop-out reason. A detailed more detailed description will be included in the SAP.

